#### Physical training

Patients in the intervention group start with a (45 min) combined in-hospital intake assessment with the physical and occupational therapist. They will assess the current physical and independence status, the limitations, and discuss personal goals following the latest Dutch CR guideline [35]. During this first assessment, the therapist and patient will determine the focus of the following consults and determine the distribution between occupational and physical follow-up. After the first assessment, the first 3 training sessions will be in-hospital and take 45–60 min each, followed by 2 live-video training sessions of 45 min each, and weekly video coaching sessions which last 20 min with occupational or physical therapist. There will be a multidisciplinary evaluation in week 10 with the occupational and physical therapist. The frequency of the coaching sessions after week 10 will be adjusted in response to the evaluation, with the expectation that 2–4 more sessions are needed in the following 7 weeks. After 18 weeks, there will be a final remote assessment with both therapists.

#### Nutrition intervention

Patients in the intervention group start with an initial video assessment with a dietician to assess and discuss dietary pattern, (unintentional) weight loss, malnutrition, and adherence to sodium and fluid restriction. Before the first consultation, the patients will fill in the NutriMáx-questionnaire based on the nutrition guideline from the Dutch Health Council for providing insight in to the actual nutritional behaviour [36]. Personalised nutrition goals will be discussed by the dietician and patient with specific attention for sodium and fluid restrictions. The nutrition behaviour will be followed during the intervention period using a chatbot, which is a web-based/mobile-based conversational dietary assessment tool used for monitoring daily dietary behaviour. There will be 3 individual video consultations with the dietician, and one group-based video consultation with other CTR participants and dietician. Before the final assessment the NutriMáx will be re-assessed.

#### Psychological intervention

Patients in the intervention group will have a video-based intake assessment with a psychologist for the screening of anxiety and depression symptoms, and the coping strategies used for managing their illness and health. In addition to this assessment, information about psychological status will be obtained from questionnaires (e.g. HADS, GAD-7, PHQ-9, DS-14). The patient and psychologist will determine whether follow-up consultation is needed, and in what form.

#### Digital platform

The study intervention will be performed using a secured, personalised, and patient-centred digital platform (‘My Flow Coach’, Mibida BV, Eindhoven, The Netherlands). The platform is used for daily monitoring of the RPM programme, and visualising the data from the wrist-worn device (Philips Health Band; PHB, Philips Electronics Nederland B.V., Eindhoven, The Netherlands) directly after hospital discharge. The platform has features that enable patients to:Register and evaluate vital parameters, and HF related complaints for daily monitoringRegister and evaluate physical, nutritional, and mental health rehabilitation goals (intervention group)Register treatment modules (intervention group)Upload and review data from the wrist-worn device (e.g. heart rate, steps, active minutes, energy expenditure)Perform video- and chat consultations with health care providersProvide relevant caregivers (e.g. cardiologist, specialised cardiac nurse, physical therapist, occupational therapist, dietician, psychologist, investigator) access to relevant clinical data.

### Wrist-worn device

All study participants will receive a wrist-worn device (PHB) at hospital discharge for continuous data collection (e.g. activity counts, heart rate, respiration rate, total energy expenditure, active energy expenditure, steps, and sleep). The PHB provides continues health tracking by measuring the movement and physiological parameters by photoplethysmography technology (PPG). The measurements will be transferred to an application on their mobile phone or tablet via Bluetooth, and to the Philips Actigraphy Server System (PASS). The data will be collected and saved using a study ID (identification) code, and is only accessible by the research team. Participants get access to their raw data in the mobile application and digital platform. They will be asked to wear the wrist-worn device preferably 24 h a day, but at least during every exercise moment. The data will be collected from hospital discharge until 6 months after randomisation.

### Chatbot

The chatbot application (Mibida BV) will monitor the daily dietary behaviour of the intervention group during the intervention period. The patients will regularly receive multiple choice questions from the chatbot about their intake (e.g. ‘Goodmorning, what did you eat this morning?’) (Fig. 2; Chatbot schedule). The chatbot has the intention to trigger ‘nudging’ based on the Nudge Theory [37], which refers to strategically changing the environment to anticipate on altering peoples’ behaviour without forbidding any options. The chatbot is accessible with an application on a mobile phone or tablet for the intervention group during the intervention period. The data entered by the patients will be visible for the dietician on the digital platform.

**Fig. 2 Fig2:**

Chatbot schedule – repeated every 4 weeks. Weekdays – Monday to Sunday. X = measuring day

### Control group

Both the control and intervention group will continue to use the RPM programme during the study period, given this is part of regular care, and outpatient appointments with the cardiologist and specialised HF nurse will be planned when needed.

### Outcome measures

The primary outcome measure is physical functional capacity at randomisation, 18 weeks and 6 months after randomisation. Secondary outcome measures are recovery after submaximal exercise, maximal exercise capacity, subjective health status and quality of life, personality and behaviour aspects, nutrition behaviour, compliance and acceptance to the intervention, fluctuation of congestive HF biomarkers, and readmission rate.

### Physical functional capacity

Physical functional capacity is assessed with the Short Physical Performance Battery (SPPB) functional test. The SPPB is an objective assessment tool to evaluate the lower extremity function in older persons to reflect the physical self-reliance. It is described as a screening tool to detect frailty [38], and a predictor of major adverse health-related events (e.g. disability, hospitalisation and mortality) in elderly patients [39–41]. The test consists of three parts: gait speed, standing balance and time to rise from a chair. Each test is scored out of 4 points; 0 corresponds with not able to perform the test, and 4 with best performance. A maximum of 12 points can be scored, 0–3 corresponding with severe physical limitation, 4–9 high risk, and 9–12 low risk for developing new physical limitations.

### Maximal exercise capacity and recovery after submaximal exercise

All patients will start the intervention period with a symptom limited maximal Cardiopulmonary Exercise Test (CPET) on a cycle ergometer (Lode Corival, Groningen, The Netherlands) using an individualised ramp protocol aiming of a total test duration of 8–12 min. CPET will be used to determine the maximal exercise capacity and the peak workload, to support the prescription of a tailored exercise rehabilitation programme [42, 43]. The effect of the intervention on maximal exercise capacity, defined as VO_2peak_, will be evaluated with the validated FitMáx©-questionnaire at randomisation, and follow-up [44]. Furthermore, recovery of O_2_ kinetics (τ-rec) after submaximal exercise will be assessed with a Constant-Load Exercise Test (CLET) at 50% of the peak workload at randomisation and follow-up. The CLET includes 2 min of rest, 2 min of unloaded pedalling, 6 min at 50% of the maximum workload, and a resting period of at least 5 min until reaching or approaching the VO_2_ baseline value. Submaximal oxygen uptake kinetics are found to be equally related to functional mobility in elderly and HF patients as VO_2peak_ [45]. CHF patients consume oxygen at a higher level to their peak oxygen uptake than healthy subjects during activities of daily life (ADL), Spruit et al. found a VO_2_ of 38–52% of the peak VO_2_ during ADL [46]. Therefore, CLET at 50% of the peak workload is expected to be indicative of ADL activities, and better tolerated and more representative for changes in physical capacity than maximal exercise [47].

### Frailty risk screening

Frailty has been defined as a clinical syndrome with declines in multiple physiological systems associated with increased vulnerability to stressors related to adverse outcomes, such as disability, falls, hospitalisation, and mortality [48]. Although an universal consensus about an appropriate and accessible screening tool is lacking, the prominent domains are found in the Vigorito frailty assessment tool [49]. In this study, a global frailty screening will be made based on this Vigorito frailty assessment tool [50] using the following domains:Physical activity and function; evaluated with SPPB and Handgrip Strength test (HGS) at randomisation, and follow-up;Malnutrition; evaluated with SNAQ (Short Nutritional Assessment Questionnaire) for malnutrition screening at inclusion;Cognitive impairment; evaluated with MoCA (Montreal Cognitive Assessment) at randomisation;Comorbidities and medication use; evaluated with the number of medications used at inclusion (hospital discharge);Physiological and social status; evaluated with the depression and anxiety screening questionnaires HADS (Hospital Anxiety and Depression Scale), GAD-7 (Generalised Anxiety Disorder assessment) and PHQ-9 (Patient Health Questionnaire) at randomisation, and follow-up.

### Subjective health status and quality of life

Health related quality of life (HRQoL) is evaluated with the KCCQ-12 (Kansas City Cardiomyopathy Questionnaire), and MLHFQ (Minnesota Living with Heart Failure Questionnaire). KCCQ-12 is the shorter version of the self-administered KCCQ, and is assessed to measure patients’ perception on their health status. It includes the frequency of HF symptoms, physical and social limitations, and quality of life (QoL) impairment as a result of HF within a 2-week recall period. The MLHFQ is a 21-item, self-administered instrument developed to independently measure the effect of HF on patients’ lives (in the physical, socio-economic and emotional/physiological domain) over the previous 4 weeks [51]. The KCCQ and MLHFQ are both reliable and validated questionnaires responsive to clinical change, however the KCCQ is more strongly correlated with functional status parameters, and MLHFQ more responsive to improvement in physical functional capacity (6MWT) [52, 53].

### Personality and behaviour aspects

Self-care behaviour and personality characteristics are evaluated with questionnaires to evaluate its influence on the primary outcome. Personality is evaluated with the DS-14 (Type D personality scale), and premorbid behaviour with the PLF (Premorbid Lifestyle questionnaire). Illness perception and self-care behaviour are evaluated using the IPQ (Illness Perception Questionnaire) and EHFScBS (European Heart Failure Self-Care Behavior Scale).

### Nutrition behaviour

Nutrition behaviour is assessed with the NutriMáx-questionnaire based on the Dutch dietary guideline of the Dutch Health Council [36]. NutriMáx consists of 18 questions that will provide an overview of the nutrition behaviour based on the 15 nutrition categories listed in the national nutrition guideline. The total score is scaled from 0 – 32, and represents the adaptation to the guideline. A score of 28 – 32 represents good adaptation, 20 – 27 moderate adaptation, and 19 or below poor adaptation.

### Compliance and physical activity

The data collected by the PHB and stored at PASS is used to determine the compliance and physical activity. Compliance will be evaluated in terms of: (i) the time of wearing the wrist-worn device, (ii) and achievement of the personalised physical goals set by the therapist for the rehabilitation group. Physical activity will be evaluated during the different study phases by change in active and total energy expenditure, and step counts in both groups. Medication adherence and subjective activity level is evaluated with the MMAS-8 (Morisky Medication Adherence Scale) and self-constructed 1-question activity questionnaire.

### Acceptance of the intervention and platform

Satisfaction and acceptance of the CTR programme in general, the chatbot application, and digital platform is assessed using a questionnaire based on the 5-point Likert scale. The control group will only evaluate the satisfaction and acceptance of the digital platform.

### Readmission rate and other adverse events

The readmission rate and other adverse events are assessed during the study period in both groups. Readmission is defined as a hospitalisation for at least 24 h. We will differentiate between HF related causes, other cardiovascular causes, and non-cardiovascular causes of readmission. Other adverse events that will be reported are: 1) acute decompensation without hospital admission, 2) myocardial infarction, 3) emergency room visit without hospitalisation, 4) (cardiac) surgery, 5) admission to a nursing home or rehabilitation centre, 6) (cardiovascular) death, and 7) adverse events that might be related to the intervention.

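### Falls, exercise-type injuries, syncope and symptomatic arrhythmia that trigger no other listed event are reported only if possibly intervention-related, so this subset of harms cannot be compared between arms

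*Protocol article*

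**What the plan says.** The section *Readmission rate and other adverse events* of the protocol article opens with a symmetric statement: "The readmission rate and other adverse events are assessed during the study period in both groups". It then sets out what is reported.

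- Readmission has a duration threshold ("Readmission is defined as a hospitalisation for at least 24 h") and is classified by cause: "We will differentiate between HF related causes, other cardiovascular causes, and non-cardiovascular causes of readmission".
- Items 1 to 3 are "1) acute decompensation without hospital admission, 2) myocardial infarction, 3) emergency room visit without hospitalisation".
- Items 4 to 6 are "4) (cardiac) surgery, 5) admission to a nursing home or rehabilitation centre, 6) (cardiovascular) death".
- The last item is "7) adverse events that might be related to the intervention".

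Falls, injuries, syncope and arrhythmia are not named as events. *Frailty risk screening* does name falls, describing frailty as "increased vulnerability to stressors related to adverse outcomes, such as disability, falls, hospitalisation, and mortality".

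Under *Study design*, controls receive remote patient management (RPM) without cardiac telerehabilitation (CTR). Under *Randomisation, blinding and treatment allocation*, participants, the investigator and other medical professionals know the allocation. A blinded investigator is mentioned only for the Short Physical Performance Battery (SPPB) and the handgrip test.

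**The concern.** A relatedness condition on entry to the event list behaves differently in the two arms. A stumble or muscle strain in a CTR patient who trains at home can readily be called possibly related. The same event in a control has no exercise programme to be related to. The count then mixes true harm with the effect of the filter, and there is no background rate to set it against.

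This matters in this trial because the Discussion stresses that frail elderly patients are not excluded, and the training moves to home video sessions and coaching after three in-hospital sessions. The primary outcome tests balance, gait speed and chair rise, so readers will ask whether minor falls went up or down. With the list as written, an increase could not be separated from background and a decrease could not be seen.

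**Working it through.** The plan states no figure on this point, so the check is mainly textual.

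**1. Which categories carry a causal condition?** Readmission plus items 1 to 7 makes eight reported categories. Readmission and items 1 to 6 are defined by what happened, with no reference to cause as a condition of entry: 1 + 6 = 7 of 8. Only item 7 is defined by suspected cause.

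**2. What route does a fall take?**

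| Consequence of the fall | Route | Same rule in both arms? |
|---|---|---|
| Hospital stay of at least 24 h | Readmission, non-cardiovascular | Yes |
| Emergency room visit, no admission | Item 3 | Yes |
| Operation | Item 4 | Yes |
| Nursing home or rehabilitation centre | Item 5 | Yes |
| Death | Item 6 | Yes |
| None of these | Item 7, if judged possibly related | In practice CTR arm only |

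Injury, syncope and symptomatic arrhythmia follow the same routes.

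**3. Can a control meet item 7?** If the intervention means CTR, as *Study design* implies by labelling CTR plus RPM the intervention group, a control event has nothing to be related to. If it is read to include RPM, which both arms receive, a fall at home would still hardly qualify. The article does not say who judges relatedness, but the only blinded role it describes is for the two functional tests.

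**4. Is detection equal?** Both arms share daily RPM entries with five heart failure questions, nurse review, routine remote follow-up at 2 and 6 weeks after discharge and every 3 months, and the study assessments at 18 weeks and 6 months. The sentence "outpatient appointments with the cardiologist and specialised HF nurse will be planned when needed" also covers both arms. The CTR arm has further scheduled contacts:

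- general intake 1
- therapist intake 1
- in-hospital sessions 3
- video sessions 2
- week-10 evaluation 1 (counted as a patient contact)
- final assessment 1
- dietician 4 (3 individual and 1 group)
- psychologist intake 1

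The sum is 1 + 1 + 3 + 2 + 1 + 1 + 4 + 1 = 14. The 2 to 4 later sessions that the article expects bring it to 16 to 18, and weekly coaching comes on top. Controls are closely followed, but through heart failure questions. The CTR arm has more occasions on which a fall would come up.

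**5. How many patients might be affected?** The documents give no rate. Assume that a proportion p of patients in each arm has such an event, with 64/2 = 32 per arm. The expected number per arm is 32p, and the 95% half-width for the between-arm difference under symmetric recording is 1.96 × √(2p(1 − p)/32).

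| Assumed p | Expected per arm | Half-width |
|---|---|---|
| 0.10 | 3.2 | 1.96 × 0.075 = 14.7 points |
| 0.20 | 6.4 | 1.96 × 0.100 = 19.6 points |
| 0.30 | 9.6 | 1.96 × 0.115 = 22.5 points |

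Symmetric recording would therefore support a descriptive comparison, not a precise one.

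**The case against.** The strongest reply is that the article assesses events in both groups, and that any fall with a serious consequence enters through readmission or items 1 to 6 in either arm. This stands. A reader might infer from item 7 that no comparison of harms between arms is possible, but the list does not support that: seven of eight categories are comparable. Serious falls would be counted in both arms, though not labelled as falls.

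Second, the article lists what will be reported and does not say that other events go unrecorded. A full protocol, not shown here, may define and collect adverse events more widely. This also stands as a caution: it is not established that a control's fall leaves no trace in the database. It does not remove the point, because the article is not silent. It states a reporting rule with a causal condition, and that rule is one-sided.

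Third, item 7 refers to the intervention without defining it, and the article sometimes uses the word for the combined RPM and CTR programme. A strict zero in controls is therefore not fixed by the text. It is the likely result for exercise-type events.

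Fourth, two further inferences fail. Table 2 lists untreated life-threatening arrhythmia and advanced atrioventricular block as exclusion criteria, not as risks of the programme. Nor do the documents say that a better SPPB score reduces falls: they link falls to frailty, and SPPB to disability, hospitalisation and mortality.

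Finally, falls are not a stated outcome, and adding them could be called a preference about safety scope. That has some force, but item 7 already intends to capture harms of the programme and does so in a form that has no comparator.

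**Conclusion.** The concern holds for a defined subset: falls, exercise-type injuries, syncope and symptomatic arrhythmia that lead to neither readmission nor any of items 1 to 6. These reach the report only through a relatedness judgement by people who know the allocation, and in practice only the CTR arm can satisfy it. That subset cannot be compared between arms. Readmission and items 1 to 6 can.

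The affected part is one category of eight, covering the less serious events. Their number cannot be derived from the documents; the assumed range above is only a scale. The conclusion rests on reading the article's list as the reporting rule and the intervention as CTR. It does not touch the primary analysis. It is worth correcting because a one-sided count is easily read as harm and the correction is cheap.

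**What to change.** Add falls and injuries, with syncope and symptomatic arrhythmia, to the numbered list as events recorded in both arms whatever the suspected cause. Ask both arms the same fixed questions about them at the existing 18-week and 6-month assessments, so that the comparison does not depend on the extra CTR contacts. Record possible relatedness afterwards as an attribute of each event, and tabulate all such events by arm. If the full protocol already collects them this way, correct the article's list to say so.

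The cost is a short checklist at two existing visits, a revised sentence in the protocol, and a few more event entries, mostly in the control arm. No visit is added and no treatment changes. With 32 per arm the comparison should be presented as descriptive.

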### Heart failure biomarkers

HF related biomarkers (NTproBNP and GDF15) are measured to evaluate the effect of CTR on fluctuation of these biomarkers, and the predictive value of these markers on physical functional capacity, readmission, and mortality. N-terminal prohormone of BNP (NTproBNP) is a reliable gold standard diagnostic biomarker in HF, and has high prognostic accuracy for death and HF hospitalisation [54]. Growth Differentiation Factor 15 (GDF15) is a less known biomarker, although multiple studies have provided evidence of its prognostic value in CHF patients [55, 56]. These biomarkers are determined at 6 different moments in the study: (I) the first day of the initial hospital admission, (II) at hospital discharge, (III) 1–2 weeks after hospital discharge, (IV) when ‘stable HF’ is reached, (V) 18 weeks after randomisation, and (VI) 6 months after randomisation.

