### Randomisation, blinding and treatment allocation

Participants are randomly allocated to the intervention or control group (1:1) after reaching stable HF and completing the first measurements. Participants will be replaced when discontinuing from study protocol before randomisation. Randomisation is performed by the investigator using a computerised randomisation system in the web-based database software Castor EDC (Castor Electronic Data Capture, Ciwit BV, Amsterdam, The Netherlands). The computer system uses variable block sizes (2,4) stratified for age (< 75 years or ≥ 75 years) and left ventricular ejection fraction (LVEF ≤ 40%, LVEF 41 – 49% or LVEF ≥ 50%) for randomisation. Overall, patients with HF are elderly with an average age of 75.2 years in Western Countries as presented by Norhammar et al. [33]. The participants, investigator, and other medical professionals will not be blinded for the treatment allocation due to the nature of the intervention. For the assessment of the functional tests (Short Physical Performance Battery and Handgrip Strength test) a blinded investigator will be involved.

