### Statistical analysis

All analyses will be performed according the intention-to-treat principle. Descriptive statistics will be used to present demographic and baseline characteristics. Between- group differences in the primary and secondary endpoints will be analysed by the unpaired T-test for continuous variables and by a chi squared test for categorical variables. A paired T-test will be used to evaluate within-group differences for the primary endpoint.

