### Sample size calculation

The sample size calculation is based on the primary outcome measurement – physical functional capacity assessed by the SPPB. Assuming that the study population in general corresponds with lower performance (SPPB score ≤ 9), and that CTR will result in an increase of 1.6 points (SD 2.17) as described by Rengo et al., 64 patients are needed to achieve a statistical power of 0.80 [57]. Previous research found a subjective and quantitative better physical functional capacity with an increase of 0.4 – 1.5 points [58].

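### The effect of CTR on NT-proBNP and GDF15 is assigned an unadjusted t-test, although the value at stable HF and the randomisation strata are available as covariates

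*Protocol article*

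**What the plan says.** - **Outcome.** The Outcome measures section lists "fluctuation of congestive HF biomarkers, and readmission rate" among the secondary outcomes. The Heart failure biomarkers section says that NT-proBNP and GDF15 are "measured to evaluate the effect of CTR on fluctuation of these biomarkers". It also gives a second purpose: their predictive value for functional capacity, readmission and mortality.
- **Sampling.** "These biomarkers are determined at 6 different moments in the study". The fourth is "IV) when ‘stable HF’ is reached"; the fifth and sixth are at 18 weeks and 6 months after randomisation.
- **Allocation.** Patients are "randomly allocated to the intervention or control group (1:1) after reaching stable HF and completing the first measurements", in blocks stratified by age (two classes) and LVEF (three classes).
- **Test.** The Statistical analysis section says that between-group differences in the "primary and secondary endpoints will be analysed by the unpaired T-test for continuous variables". It makes no exception for the biomarkers and names no covariate, no scale, and no choice between follow-up value and change.

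**The concern.** An unpaired t-test has no term for a baseline value or for strata. Of the six samples, only the last two can show an effect of CTR. The fourth, taken at stable HF, is the natural baseline: it comes after up-titration to optimal medical therapy and immediately before allocation. If a patient's marker level then predicts the later level, leaving it out keeps between-patient variation in the error term that could be removed without cost. With 64 patients in all, that matters for whether a secondary biomarker effect can be estimated with useful precision. The age and LVEF strata were judged important enough to balance at randomisation, and they too are absent from the comparison.

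**Working it through.** **Inputs from the article.** There are 64 patients randomised 1:1, so 32 per arm. This number was set for the SPPB ("CTR will result in an increase of 1.6 points (SD 2.17"), not for the biomarkers. The article states no power, mean, SD or correlation for either marker, so there is no biomarker figure to reproduce.

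**Assumptions, none from the article.** The markers are log-normal (right-skewed). The SD on the log scale is 0.4 to 1.2. The correlation r between log values at stable HF and at follow-up is 0.5 to 0.8. The true ratio of geometric means is 0.6 or 0.7. The test is two-sided at 0.05, with no missing values.

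**Formula on the log scale.** The standard error of the arm difference is SD × √(2v/32), where v depends on the analysis:
- follow-up value: v = 1
- change from stable HF: v = 2(1 − r)
- ANCOVA on the value at stable HF: v = 1 − r²

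The ratio of the ANCOVA variance to the change variance is (1 + r)/2. It is below 1 whenever r is below 1, so ANCOVA is the more precise apart from one lost degree of freedom.

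**Numbers for SD 1.0, r = 0.7, ratio 0.6.** |ln 0.6| = 0.511.
- Follow-up: v = 1, SE = 0.250, 0.511/0.250 = 2.04, power 0.52
- Change: v = 0.60, SE = 0.194, 0.511/0.194 = 2.64, power 0.74
- ANCOVA: v = 0.51, SE = 0.179, 0.511/0.179 = 2.86, power 0.80

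Simulation (20,000 trials) gives 0.52, 0.74 and 0.80 for these. It gives 0.37 for a t-test on raw follow-up values and 0.36 for one on raw change.

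**Range by simulation, ratio 0.7:**

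| Log-SD | r | Raw follow-up t | Log-change t | Log ANCOVA |
|---|---|---|---|---|
| 0.4 | 0.5 | 0.93 | 0.94 | 0.98 |
| 0.4 | 0.8 | 0.92 | 1.00 | 1.00 |
| 0.8 | 0.5 | 0.33 | 0.41 | 0.52 |
| 0.8 | 0.7 | 0.33 | 0.62 | 0.69 |
| 0.8 | 0.8 | 0.33 | 0.80 | 0.83 |
| 1.0 | 0.5 | 0.20 | 0.29 | 0.36 |
| 1.0 | 0.7 | 0.20 | 0.44 | 0.49 |
| 1.0 | 0.8 | 0.20 | 0.60 | 0.64 |
| 1.2 | 0.5 | 0.13 | 0.21 | 0.27 |
| 1.2 | 0.7 | 0.13 | 0.32 | 0.37 |
| 1.2 | 0.8 | 0.13 | 0.46 | 0.49 |

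At log-SD 0.4 the gain over the raw follow-up test is at most about 8 points. At log-SD 0.8 to 1.2 the gain over a log-change test is about 3 to 11 points.

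**Type I error** at log-SD 1.0 and r = 0.7: about 0.04 for the raw t-tests, 0.05 for the log t-tests and 0.05 for log ANCOVA.

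The simulation contains no strata, so it says nothing about what adjusting for age and LVEF would add.

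**The case against.** Several stronger readings are tempting, and the article does not support them.

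- **That the test will be run on raw concentrations.** A reader might infer this from an unqualified t-test. But no scale is named, and a t-test on log values or log change fits the text. Transforming a laboratory marker is a detail that a condensed article may leave to the analysis plan, which is not shown.
- **That the value at stable HF will not be used at all.** The outcome is worded as fluctuation, which may well mean change. A change score does use the earlier value, though less efficiently than ANCOVA. What the text does support is that no covariate is named.
- **That much of the power is lost.** The contrast of 0.37 with 0.80 pairs the recommended method with one of the least favourable readings, under an assumed skew. Against log change, the same setting gives 0.74 against 0.80.
- **That the arms might be compared at the first three sampling moments.** Nothing proposes this, and those samples can serve the stated predictive purpose.

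It is also fair to say that the type I error is not inflated, that the trial claims no power for this question, and that the missing covariate is a feature of the general rule rather than something peculiar to the biomarkers.

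What stands is that the rule as written is an unadjusted test. In every setting run, log ANCOVA had power at least as high as each t-test that the wording allows.

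**Conclusion.** The point holds as a matter of efficiency. The article fixes an unadjusted unpaired t-test for a secondary question for which a baseline value and stratification factors are already collected. Adjustment improves a method that the article states; it does not fill in a detail that the article left out.

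The size depends on which t-test is meant and on assumptions that the article cannot confirm. For a log-change test it is a few points, up to about 11. For a raw follow-up test it is at most about 8 points at log-SD 0.4, rising to about 43 points (0.80 − 0.37) at log-SD 1.0, correlation 0.7 and ratio 0.6. The validity of the test is not in question, and no stated figure is contradicted.

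**What to change.** In the Statistical analysis section, add a sentence for the biomarkers. At 18 weeks and at 6 months, the arms are compared by ANCOVA on the log-transformed marker. The covariates are the log value at stable HF, age class and LVEF class, and the result is a ratio of geometric means with 95% CI. The sentence also settles what is tested under the word fluctuation: the follow-up level, given the level at stable HF.

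The cost is wording only, with no extra samples, visits or patients. Age and LVEF as main effects take 1 + 2 = 3 degrees of freedom, which 64 patients can bear. Results will read as ratios rather than as differences in concentration.
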